# Abdominal Septic Shock – Endotoxin Adsorption Treatment (ASSET) – endotoxin removal in abdominal and urogenital septic shock with the Alteco® LPS Adsorber: study protocol for a double-blinded, randomized placebo-controlled trial

**DOI:** 10.1186/s13063-016-1723-4

**Published:** 2016-12-08

**Keywords:** Septic shock, Endotoxins, Hemoperfusion, Gram-negative bacteria

## Abstract

**Background:**

Severe sepsis and septic shock are common in intensive care and carry high mortality rates. In patients with Gram-negative infections, early and extensive removal of endotoxin may limit the inflammatory response that characterizes septic shock. The Alteco® LPS Adsorber (hereafter referred to cited as the lipopolysaccharide (LPS) Adsorber) can be used for endotoxin removal and attenuate the deleterious inflammatory and clinical responses seen in septic shock.

**Methods/design:**

The Abdominal Septic Shock – Endotoxin Adsorption Treatment (ASSET) trial is a pilot study investigating the feasibility and safety of LPS Adsorber therapy. This pilot, multicenter, stratified, parallel, double-blinded, randomized, phase IIa, feasibility clinical investigation will be performed in five Scandinavian intensive care units. Thirty-two subjects with early septic shock and organ failure, following adequate resuscitation, will be randomized to receive either: extracorporeal veno-venous hemoperfusion therapy with the LPS Adsorber or veno-venous hemoperfusion therapy with a placebo adsorber (without active LPS-binding peptide). Patients will be stratified by infection focus such that 20 subjects with an abdominal focus (stratum A) and 12 subjects with a urogenital focus (stratum B) will be included in a parallel design. Thereafter, an interim analysis will be performed and an additional 12 patients may be included in the study. The study is designed as adaptive a priori: the patients from this study can be included in a later phase IIb study. The aim of the study is to investigate the feasibility of LPS Adsorber therapy commenced early in the time-course of septic shock. The primary endpoint will be a characterization of all reported unanticipated serious adverse device effects and anticipated serious adverse device effects. Secondary outcomes are decrease in endotoxin plasma concentration, impact on clinical outcome measures and impact on inflammatory response by LPS Adsorber therapy, as well as detailed description of the relevant mediators bound to the LPS Adsorber. Recruitment of patients will start in September 2015.

**Discussion:**

The ASSET trial will give insight into the feasibility and safety of this LPS Adsorber therapy and preliminary data on its potential clinical effects in septic shock. Moreover, this pilot trial will provide with necessary data for designing future studies.

**Trial registration:**

ClinicalTrials.gov Identifier NCT02335723. Registered on 28 November 2014.

## Background

Although severe sepsis and septic shock are common in intensive care and carry high mortality rates no specific treatment has been established to counteract the associated inflammatory response. Current management may be considered supportive only and consists mainly of effective antimicrobial therapy, removal or drainage of infections (source control) and support of failing organs [1]. Therefore, development of new treatment methods for sepsis and septic shock is crucial for medical, humanitarian and health-economic reasons.

Endotoxins are molecules found in the outer membrane of the cell wall in Gram-negative bacteria. They are potent activators of the inflammatory system through the innate immune system and are presumably the key triggers of the systemic inflammatory response [2–4]. Hence, attenuating the effect of endotoxins seems to be a logical and desirable strategy in the treatment of severe sepsis and septic shock. However, so far the use of anti-endotoxin strategies has been disappointing [5–8]. On the other hand, adsorber therapy was proven beneficial in early sepsis patients due to intra-abdominal infections and added substantially to improved outcome in conjunction with conventional interventions. Improved outcome was associated with reduced endotoxin levels in blood [9, 10]. Therefore, it is reasonable to hypothesize that using adsorption membranes in the treatment of selected Gram-negative septic shock in the early phase, with a strictly defined time-frame since the onset of clinical symptoms, may offer therapeutic benefits. Several extracorporeal endotoxin-removal devices, based on various endotoxin-binding mechanisms, have been investigated with diverging results [9, 11, 12]. Currently, at least one trial is investigating the effect of endotoxin removal with polymyxin B cartridges [13].

Another endotoxin removal device based on a different concept is a novel, high-capacity adsorber system (from Alteco® Medical AB, Lund, Sweden) with a high-endotoxin-affinity-peptide endotoxin-binding mechanism (hereafter referred to as the lipopolysaccharide (LPS) Adsorber) that has been clinically available for some years. This adsorber putatively binds endotoxin and thus decreases endotoxin load in patients with Gram-negative sepsis. Case reports and series from patients with septic shock suggest that endotoxin removal could be achieved in clinical practice with LPS Adsorber [14, 15]. However, no randomized controlled trial has investigated the potential benefits of this LPS Adsorber. LPS Adsorber is described as biocompatible and no specific side effects related to it have been reported.

We hypothesized that in patients with Gram-negative infections, early and extensive removal of endotoxin may limit the inflammatory response that characterizes septic shock. This LPS Adsorber can be used for endotoxin removal and, in this way, add to the currently available strategies for sepsis treatment.

The present clinical investigation aims to collect information on the feasibility and safety of LPS Adsorber therapy in patients with septic shock of presumed abdominal or urogenital origin. Secondary aims are to report the performance of the LPS Adsorber. Specifically, we wish to study the extent of endotoxin removal by the LPS Adsorber, its effects on organ failure development and the extent of organ support, as well as its possible impact on the inflammatory response.

This trial should contribute to new knowledge since it investigates a high-capacity peptide-binding-based endotoxin removal that can be run for longer periods and at higher blood flow that other endotoxin adsorbers. Moreover, unlike in other device trials, the LPS Adsorber will be compared to an identical LPS Adsorber cartridge without active LPS-binding peptide. Thus, a double-blinded randomized controlled trial will be possible to perform.

Finally, the ultimate objective of this pilot investigation is to provide the necessary information on the magnitude of the clinical effects of the LPS Adsorber, thus providing the basis for further investigations in a larger population.

## Methods/design

This is a pilot, multicenter, stratified, parallel, double-blinded, randomized, phase IIa, feasibility clinical investigation and is reported according to the Standard Protocol Items: Recommendations for Interventional Trials (SPIRIT) guidelines [16]. Subjects will be enrolled in accordance with an adaptive design, with an interim analysis allowing enrollment of additional patients until an adequate sample size is attained, to show the safety and the feasibility or lack thereof of LPS Adsorber therapy in the target patient population.

The study will be conducted in five general intensive care units (ICU) in Uppsala, Sweden, Bergen and Oslo, Norway, and Tampere and Kuopio, Finland. These ICUs will be screened around the clock to identify potential patients. Initially, 32 subjects admitted to the ICU with confirmed septic shock will be stratified in accordance with the origin of their suspected endotoxemia, i.e., 20 septic shock subjects with an abdominal focus (stratum A) and 12 subjects with a urogenital focus (stratum B) will be randomly allocated to the active LPS Adsorber group (Interventional Medical Device group, IMD group): current best practice in combination with LPS Adsorber therapy *or* placebo device group (control group): current best practice in combination with placebo adsorber therapy (identical LPS Adsorber cartridge without active LPS-binding peptide). The random allocation to either therapy arm in each stratum will be performed in a 1:1 ratio.

An interim analysis will be performed after all subjects in their corresponding stratum have completed their participation in the investigation to reveal whether 12 additional subjects are required. The enrollment plan in the clinical investigation is summarized in Fig. 1.

**Fig. 1 Fig1:**
[figure not shown]
Enrollment plan for each stratum and interim analysis. *Optional enrollment of sepsis subjects (of abdominal, urogenital or both origins) after interim analysis

The study has an adaptive design and thus the investigators have made an a-priori decision to include the patients from this study in a later phase IIb study aiming to investigate and report possible outcome benefits of the therapeutic intervention.

### Inclusion criteria

Upon enrollment (i.e., pretreatment phase), subjects admitted to the ICU with suspected endotoxemia will be screened for fulfillment of the “Illness severity criteria” confirming early stage severe sepsis.

Within 6 h of enrollment, subjects who also fulfill the “Treatment criteria” confirming septic shock will be eligible for randomization.

The subjects have to meet all of the following criteria to be eligible to enter the clinical investigation:

#### Illness severity criteria

At enrollment, subjects must meet the inclusion criteria #1 through #5 listed below to be eligible to enter the clinical investigation:Subjects must have suspected infection of abdominal or urogenital origin for which the subject is receiving intravenous antimicrobial therapySubjects must have systemic inflammatory response syndrome (SIRS), i.e., they must meet at least two of the criteria defined below during the 36 h prior to clinical investigation entry:Abnormal body temperature:i.)Fever: core temperature (measured via rectum, urinary bladder, central catheter) above 38 ° C (100.4 ° F), *or*
ii.)Hypothermia: core temperature (measured via rectum, urinary bladder, central catheter) below 36 ° C (96.8 ° F)
Heart rate above 90 beats/minSpontaneous respiratory rate above 20 breaths/min *or* PaCO_2_ < 32 mmHg (4.3 kPa) *or* concurrent use of mechanical ventilation for an acute processWhite blood cell count (WBC) of >12,000 cells/mm^3^ or <4000 cells/mm^3^
*or* a >10% increase in immature neutrophils
Subjects must have clinical signs consistent with organ dysfunction, i.e., they must meet at least one of the following criteria during the 6 h prior to clinical investigation entry:Subjects, independent of gender, must be aged 18 years or olderSubjects or legally acceptable representatives, as appropriate, are willing and able to provide signed informed consent

#### Treatment criteria

6.Prior to randomization, subjects must meet all inclusion criteria (#7 through #11) listed below to be assigned to a treatment group:7.Subjects must have septic shock according to the modified septic shock criteria, i.e., Illness severity criteria #1 through #3 are still fulfilled8.Subjects must score a Sequential Organ Failure Assessment (SOFA) score of 10 or higher, *and* a Simplified Acute Physiology Score (SAPS II) of 58 or higher9.Appropriate vascular access must have been obtained10.Subjects must have received ≥30 mL/kg of intravenous fluid within the 6 h prior to randomization11.Subjects must have a continuous requirement for vasopressor support (at least one of the vasopressors must be given as listed below) for at least 2 h prior to randomization to maintain mean arterial pressure (MAP) >65 mmHg or systolic arterial pressure >90 mmHg with reasonable attempts made to wean the subject from vasopressor support. Careful evaluation is made so that vasopressor dependency is *not only* related to sedation. Required vasopressor support includes at least one of the following vasopressors administered as described below (and allows for combination therapy where other vasopressors are given with modified administration regimen):Norepinephrine ≥0.07 μg/kg/minDopamine ≥10 μg/kg/minPhenylephrine ≥35 μg/kg/minEpinephrine ≥0.07 μg/kg/minVasopressin ≥0.03 units/min

12.Subjects must be able to initiate the clinical investigation intervention within 12 h of fulfillment of the Illness severity criteria

### Exclusion criteria

Subjects who meet any of the exclusion criteria listed below will *not* be permitted to enter the clinical investigation:Sepsis-induced organ dysfunction for longer than 12 h prior to the time point for achieving “Illness severity criteria fulfilled”Vasopressor therapy (at any dose) for longer than 8 h (not including the time spent in the operation theatre) prior to the start of the therapy with the investigational devicePreexisting irreversible medical conditions such as:○ Poorly controlled neoplasms or hematologic disease (i.e., indication of disseminated cancer outside the suspected primary tumor and hematologic disease not in remission)○ End-stage cardiac disease○ Cardiac arrest requiring cardiopulmonary resuscitation or with pulseless electrical activity or asystole within the past 7 days○ End-stage lung disease; end-stage liver disease○ HIV/AIDS with known end-stage processes○ Other uncorrectable medical condition(s) deemed by the clinical investigator to hinder the subject to adhere to the fulfillment of the activities described in the Clinical Investigation Plan (CIP)
Extreme illness, i.e., subject is moribund and death is perceived to be imminent (within 24 h)Recent or current participation (≤30 days) in another interventional sepsis trialRecent or current treatment (≤30 days) with an adsorption product, including the LPS AdsorberTreatment with an investigational medicinal product for any indication within the last 30 days before enrollment in the clinical investigationPregnancyContraindications to the use heparin or protamine, as in case of, but not limited to:○ Prior heparin-induced thrombocytopenia II (HIT II)○ Prior intracranial bleeding of any cause up to 90 days before inclusion in this clinical investigation○ Prior neurosurgery up to 90 days before inclusion in this clinical investigation. Prior hemorrhagic stroke up to 90 days before inclusion in this clinical investigation○ Fish allergy
Other abdominal inflammatory conditions such as, but not limited to:○ Suspected pancreatitis (serum amylase (s-amylase) level at least three times the upper limit of normal (ULN))○ Suspected fulminant hepatitis○ Suspected gastric/duodenal ulcer-related gastrointestinal perforation
Perforation of hollow organ linked to trauma within 48 h before enrollment in the clinical investigationLaparotomy reveals isolated gastric ulcerSubjects and/or their immediate family are directly affiliated to investigative site personnel in this clinical investigation (immediate family is defined as a spouse, parent, child or sibling, whether biological or legally adopted)

### Intervention

Upon enrollment (i.e., pre-treatment phase), subjects admitted to the ICU with suspected endotoxemia will be screened for fulfillment of the “Illness severity criteria” confirming the early stages of severe sepsis. Within 6 h of enrollment, subjects who also fulfill the “Treatment criteria” confirming septic shock will be eligible for randomization. Randomization to either of the treatment groups will be performed as close as possible to the start of treatment with the LPS Adsorber or placebo device.

Treatment with the LPS Adsorber or placebo device must be initiated within 6 h (day 1) following fulfillment of the “Treatment criteria” and given for 6 h. A second device treatment will be performed 24 h after the end of the first device treatment on day 2, as long as there is no evidence that treatment with the investigational device will not be beneficial or will indicate an unnecessary risk for subjects (for example, if the subject is free of vasopressor support).

The treatment with the LPS Adsorber or placebo can be discontinued at any time on the decision of the attending physician. At least one 2-h treatment session is required to fulfill the treatment protocol.

After treatment with the LPS Adsorber or placebo is finalized (post-treatment phase), subjects will be monitored until they are ready for ICU discharge or deceased. Discharge from hospital and mortality at 28 days since enrollment will also be collected. Figure 2 and Table 1 summarize the participant timeline of the clinical investigation.

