**Fig. 2 Fig2:**
[figure not shown]
Overall clinical investigational design. *Treatment with IMD or placebo device will be repeated on Day 2, i.e. 24 h after end of treatment on day 1. ^§^ Randomization will be performed as close as possible to start of treatment start (time-point O h) on Day 1

**Table 1 Tab1:** The timeline of the study according to the Standard Protocol Items: Recommendations for Interventional Trials (SPIRIT) guidelines

Assessments	Pre-treatment phase		Treatment phase						Post-treatment phase		
	Screening		Day 1			Day 2			Days 3–6	ICU discharge	28-day follow-up
	Illness criteria	Treatment criteria	Baseline	Following start of treatment 1	End of treatment 1	Prior to treatment 2 start	Start of treatment 2	End of treatment 2			
	up to −12 h	up to −6 h	Before 0 h	0 h	6 h	Before 30 h	0 h	6 h	~48–120 h		Max 28 days
Enrollment											
Informed consent	X										
Demography, medical history	X									X	
Vital signs, organ support Assessment	X		X	X		X	X		X		
Physical examination	X		X	X	X	X	X	X	X		
Laboratory assessments	X		X	X	X	X	X	X	X		
Illness severity scoring	X	X	X	X	X	X	X	X	X	X	X
Eligibility criteria #1	X										
Eligibility criteria #2		X									
Randomization		X									
Intervention											
Investigational/placebo device treatment				X			X				
Assessments											
Laboratory assessments	X		X	X	X	X	X	X	X		
Illness severity scoring	X	X	X	X	X	X	X	X	X	X	X
Prior or concomitant therapy	X	X	X	X	X	X	X	X	X	X	
AEs			X	X	X	X	X	X	X	X	
ADEs			X	X	X	X	X	X	X	X	
Device deficiencies			X	X		X	X				
ICU-LOS										X	
Hospital-LOS											X
Mortality (ICU and 28-day)										X	X

*ADEs* adverse device effects, *AEs* adverse events, *ICU* intensive care unit, *LOS* length of stay

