### Endpoints

#### Primary endpoint

Primary endpoint is characterization of all reported unanticipated serious adverse device effects and anticipated serious adverse device effects.

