#### Secondary endpoints

Relative change from baseline in plasma endotoxin (p-endotoxin) levels during (i.e., at 2 h) and immediately after end (i.e., at 6 h) of therapy with device, on both day 1 and day 2Monitoring of clinical outcome parameters during stay at ICU:○ Relative change from baseline in SOFA score (total and organ specific) measured once daily and up to 120 h (or time for ICU discharge, whichever comes first) after start of therapy with device○ Relative change from baseline in the monitoring of renal function○ Relative change from baseline in the monitoring of liver function○ Relative change from baseline in circulatory support○ Relative change from baseline in respiratory support○ ICU mortality○ ICU length-of-stay (LOS) up to 28 days
Monitoring of clinical outcome parameters during stay at hospital following ICU discharge:○ The total extension of renal support○ 28-day mortality○ Hospital-LOS up to 28 days
Monitoring of inflammatory response biomarkers:○ Inflammatory triggers and markers○ Acute phase protein markers○ Plasma cytokines
Determination of the molecular components extracted from blood circulation and captured in the LPS AdsorberCharacterization of all reported adverse events (regardless of attribution), adverse device effects and device deficiencies

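### Scheduled adverse-event collection ends at ICU discharge or death, so the safety window varies with outcome; the post-ICU renal-support endpoint has no scheduled data source

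*Protocol article*

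**What the plan says.** All references are to the protocol article.

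- **Primary endpoint:** "Primary endpoint is characterization of all reported unanticipated serious adverse device effects and anticipated serious adverse device effects". No start or end of observation is given.
- **Intervention:** after device treatment, "subjects will be monitored until they are ready for ICU discharge or deceased". The only later items named are these: "Discharge from hospital and mortality at 28 days since enrollment will also be collected".
- **Table 1** (caption: "The timeline of the study according to the Standard Protocol Items: Recommendations for Interventional Trials (SPIRIT) guidelines"): the ADE row reads "ADEs X X X X X X X X". Its eight marks run from baseline to ICU discharge, and the AE row is the same. The row "Vital signs, organ support Assessment" is last marked at days 3–6 (about 48–120 h), and the row "Prior or concomitant therapy" at ICU discharge. The 28-day column is marked only for illness severity scoring, hospital length of stay and mortality.
- **Secondary endpoints:** ICU mortality and ICU length of stay are endpoints. "The total extension of renal support" stands in the group monitored in hospital following ICU discharge. All AEs, regardless of attribution, are also to be characterized.
- **Severe adverse reactions:** sites report serious events and serious device effects within 24 h of learning of them, however long ago they occurred. No end of follow-up is set.

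**The concern.** Safety is the main purpose of this pilot, yet the period over which harm is actively looked for is set by how long the patient stays in the ICU and whether the patient survives there. If the active device changes either, the two arms are observed for different lengths of time. Crude counts or proportions by arm could then differ with no difference in harm, or hide one that exists. The protocol also intends to carry these patients into a later phase IIb study (text following Fig. 1), so the same window would carry forward with their data.

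The renal item is a different kind of problem. An endpoint is assigned to a period for which the published schedule collects no matching data.

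**Working it through.** The protocol states no figure on this point, so there is none to reproduce. The check is a reading of the schedule followed by an illustration.

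**Step 1. Last scheduled mark per row in Table 1 (11 visit columns).**

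| Row | Last mark |
|---|---|
| AEs | ICU discharge |
| ADEs | ICU discharge |
| Concomitant therapy | ICU discharge |
| Organ support | Days 3–6 |
| Laboratory | Days 3–6 |
| Severity scoring, hospital length of stay, mortality | 28 days |

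The table and the Intervention text agree on where safety monitoring stops.

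**Step 2. Where device exposure lies.** The first session runs from 0 to 6 h. The second starts 24 h after the first ends, at 6 + 24 = 30 h, and a full 6 h session ends at 36 h. Scheduled AE/ADE collection covers both sessions in any patient still in the ICU then. The varying part of the window comes afterwards.

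**Step 3. Renal support.** The organ-support row ends at about 120 h, which is 120/672 = 18% of 28 days. From then to ICU discharge the concomitant-therapy row may hold it, since the Concomitant therapy section deals with renal replacement. From ICU discharge to day 28 no row and no text collects it. The severity score at 28 days is a single time point and cannot give a duration. The endpoint nevertheless belongs to the hospital stay after the ICU.

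**Step 4. Illustration of the window effect.** These inputs are assumptions, not protocol figures: a constant event rate h per day, identical in both arms; the same window of w days for everyone in an arm; and no events reported after the window. Then P(at least one recorded event) = 1 − exp(−h·w). For example, 1 − exp(−0.03 × 5) = 0.14. Expected patients are out of 16, from 32 patients randomized 1:1.

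| h per day | w = 5 | w = 10 | w = 28 |
|---|---|---|---|
| 0.01 | 0.05 (0.8 of 16) | 0.10 (1.5) | 0.24 (3.9) |
| 0.03 | 0.14 (2.2) | 0.26 (4.1) | 0.57 (9.1) |
| 0.05 | 0.22 (3.5) | 0.39 (6.3) | 0.75 (12.1) |

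At 0.03 per day, an arm followed for 5 days would show about 2 patients with an event and an arm followed for 10 days about 4, with equal underlying risk. A common 28-day window gives 0.57 in both, apart from deaths. This shows the direction of the effect and does not estimate its size in this trial. A constant rate suits AEs of any cause better than effects tied to two short sessions.

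**The case against.** The case on the other side has real force.

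- **Late serious events are not excluded.** The primary endpoint covers all reported serious device effects, and the reporting rule has no cut-off. A reader might infer that collection stops outright at ICU discharge. The document does not say that: such events are unscheduled. The rule sets how fast a known event is reported, though, and creates no active follow-up.
- **A reader might infer that the renal endpoint cannot be computed at all.** That goes too far. Renal support up to ICU discharge may come from the concomitant-therapy row, the endpoint list itself states an intent to monitor it later, and the full investigation plan (the article reports version 5) may give the detail. What stands is a mismatch between the endpoint and the published schedule for the period after ICU discharge.
- **A reader might put a number on the loss.** With assumed ICU stays of 5 to 10 days, 1 − 5/28 = 82% to 1 − 10/28 = 64% of 28 days would lie outside the window. Shortening an assumed stay from 8 to 6 days at a constant rate would remove 1 − 6/8 = 25% of events. The document supports neither as an estimate. It gives no expected ICU stays, never names 28 days as a safety horizon, and confines device exposure to two sessions around which effects may cluster.
- **No formal comparison is at risk.** The primary endpoint is a characterization, secondary analyses are descriptive, and there is no power calculation. This is correct, but counts set out by arm would still be read as a comparison.

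**Conclusion.** The point holds in two limited parts. First, scheduled AE and ADE collection ends at ICU discharge or death, so the observation window for the primary endpoint and for all AEs depends on outcomes of the trial. Serious events after ICU discharge enter only if a site learns of them. Second, the Secondary endpoints section conflicts with the Intervention section and Table 1 on renal support after ICU discharge, and they must be reconciled.

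The size of the distortion cannot be derived from the document. It depends on ICU stay, on deaths and on when events occur, none of which is given. It is probably smaller for device effects than for all AEs, if device effects cluster around the sessions, which is itself an assumption. The change should be made, but the point does not invalidate the trial: its analysis is descriptive and both treatment sessions fall inside the scheduled window for patients still in the ICU.

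**What to change.** 1. State one safety window for every patient. Collect serious adverse events and serious device effects, anticipated and unanticipated, to day 28 at the existing 28-day follow-up, and mark them in that column of Table 1.
2. Add the number of days of renal support since ICU discharge to the 28-day column. Confirm that the concomitant-therapy record gives the days up to ICU discharge, so that the two parts sum to the stated endpoint.
3. Report events by arm over the fixed window alongside time at risk, because death will still shorten observation.

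The cost is a small amendment, a few eCRF fields, and some record review or contact for patients who have left the ICU or the hospital. The article does not say whether the 28-day follow-up involves contact with the patient, so that effort may be more than filling in fields. Patients, treatment and sample size are unaffected.
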